## Abstract

**Background:**

Patients living with advanced cancer often benefit from palliative care. Timely referral to specialist palliative care improves quality of life and reduces potentially inappropriate end-of-life care. Despite these benefits, specialist palliative care is frequently introduced late and inconsistently. This study evaluates whether systematically offering a consultation with the hospital palliative care consultation team (PCCT) to all patients referred for radiotherapy for symptomatic bone metastases improves satisfaction with care.

**Patients and Methods:**

The Timely Integration of Palliative Care in Oncology care for patients referred for palliative RadioTherapy (TIPZO-RT) trial follows the Trials within Cohorts design and is embedded within the PRospective Evaluation of interventional StudiEs on boNe meTastases (PRESENT+) cohort. Following cohort enrollment, 246 patients will be randomized (1:1) to either the intervention or control group. Patients in the intervention group are offered a PCCT consultation, which they may accept or refrain from. Patients in the control group are not informed about the trial and continue to receive usual care. After four weeks, patient satisfaction with care (affective behavior, EORTC Satisfaction with Cancer Care core questionnaire (EORTC PATSAT-C33)) will be compared between the groups. Secondary outcomes include symptom burden, quality of life, overall survival, and palliative care utilization. Additionally, in the intervention group, patients’ experiences with the consultation are evaluated.

**Discussion:**

Integrating palliative care into oncological care for patients with advanced cancer is essential to deliver comprehensive, patient-centered care that addresses physical, psychosocial and spiritual needs. This pragmatic study may provide evidence to support timely integration of specialist palliative care for all patients with bone metastases who may benefit from specialist palliative care. Using the Trials within Cohorts design, this study generates real-world evidence on the acceptance or need for a consultation with the PCCT, while minimizing disappointment or response bias, as patients in the control group are not informed.

**Trial registration:**

ClinicalTrials.gov ID NCT06805396. Registered on 25-03-2025.

## Introduction

During their disease trajectory, patients with advanced cancer and bone metastases are confronted with a variety of complaints in multiple dimensions including physical symptoms such as pain or side effects of oncological treatments, psychosocial distress and spiritual concerns. Palliative care aims to alleviate this suffering through early identification, comprehensive assessment, and treatment across physical, psychological, social and spiritual dimensions. The overall aim of palliative care is to improve the quality of life of patients with a life-limiting illness and also of their family caregivers, and can be delivered concurrently with oncological care [1,2].

Where healthcare professionals providing care for patients with a life-threatening disease are expected to provide basic (generalist) palliative care, palliative care specialists may be consulted in case of more complex situations, such as symptom burden on multiple dimensions [3,4]. Previous studies acknowledged the importance of timely referral to palliative care specialists. Randomized trials and meta-analysis investigating integrated palliative care in oncology for patients with advanced cancer have shown that it reduces symptom burden, improves quality of life, and helps prevent potentially inappropriate care at the end of life [5–10]. In a randomized controlled trial by Zimmermann et al., patients who received early palliative care (i.e., with an estimated survival of 6–24 months) reported higher satisfaction with care, whereas satisfaction deteriorated in the standard care (control) group [8].

Satisfaction with care is an important outcome for patients with advanced cancer, as they often require multiple clinical care services. It is hypothesized that palliative care enhances patient satisfaction with care by offering a person-centered holistic approach that addresses not only physical symptoms, but also psychological, social and spiritual needs [10,11]. In a previous randomized trial, patients who received early palliative care felt supported and guided in their disease trajectory and decision-making processes [8,12]. The hospital palliative care consultation team (PCCT) was particularly valued for taking the time to navigate patients through the healthcare system and help them prepare for the future, dicussing end-of-life care options consistent with individual patient preferences.

In the Netherlands, all hospitals providing oncological care are equipped with a PCCT where physicians, nurse practitioners and nurses, all with specialist palliative care training, may be consulted. According to SONCOS (Dutch Oncology Platform) guidelines, involvement of the PCCT should be considered in case of complex problems or upon patient request [3]. Despite clear evidence supporting the benefits of early integration of palliative care, referrals to palliative care specialists remain limited and may be impeded by clinician- and patient-related barriers [13,14]. In the Netherlands in 2024, only 15% of patients with cancer received a consultation with the hospital PCCT in their last year of life [15].

Clinician-related barriers include limited awareness or understanding of palliative care, the persistent misconception that palliative care is appropriate only at the very end of life, limited recognition of palliative care needs, time constraints, and competing clinical priorities [16–18]. Patient-related barriers include limited awareness of palliative care or associating it with end-of-life care, denial of the disease’s advanced stage and maintaining unrealistic expectations about life expectancy [17–19]. Furthermore, the process and timing of referral to specialist palliative care and who should be referred are poorly defined and varies across centers and specialties [20]. Multiple studies in the last decade aimed to identify criteria for timely referral of patients with advanced cancer to specialist palliative care [21,22]. However, referral of patients who meet these criteria requires efforts from clinicians to assess patients. Systematic referral of all patients to at least identify those patients in need of specialist palliative care may be more effective to timely integrate palliative care. A pilot study suggests that offering an introductory consultation with the PCCT at the time of radiotherapy referral for patients with bone metastases is both feasible and accepted. Patients valued the consultation and most did not perceive it as occurring too early in their disease trajectory [23].

### Aims

The primary objective of the TIPZO-RT trial is to evaluate the effect of systematically offering a consultation with the hospital PCCT on patient satisfaction with care four weeks after the initiation of radiotherapy in patients with advanced cancer undergoing treatment for bone metastases, compared to usual care (i.e., not systematically offering a consultation with the hospital PCCT).

Secondary objectives include 1) assessing the effect of systematic PCCT consultation on quality of life, symptom burden and overall survival, and 2) evaluating the utilization and perceived quality of specialist palliative care services in the intervention group.

## Patients and methods

### Participants

The TIPZO-RT trial follows the Trials within Cohorts (TwiCs) design and is embedded within the PRrospective Evaluation of interventional StudiEs on boNe meTastases (PRESENT+) cohort [24,25]. PRESENT+ includes patients with bone metastases referred to the Department of Radiotherapy [25]. The TIPZO-RT trial will be conducted within the Departments of Radiotherapy and the PCCTs of the University Medical Center (UMC) Utrecht, Radboudumc Nijmegen, and Leiden University Medical Center (LUMC) in the Netherlands. In addition, the PCCTs of the Meander Medical Center, Alrijne Hospital Leiden, and Groene Hart Hospital will participate in the study.

To be eligible to participate in the TIPZO-RT trial, patients must have provided broad informed consent for PRESENT + , including informed consent for use of clinical data for research, collection of patient-reported outcomes, and randomization into future trials (Fig 1). Patients will be excluded from participation if they 1) are unable to understand the study objectives, 2) lack the cognitive capacity to participate, or 3) previously had contact with the hospital PCCT.

**Fig 1 pone.0349792.g001:**
[figure not shown]
SPIRIT participant timeline: Schedule of enrollment, interventions, and assessments.

### Study design

The TwiCs design offers a pragmatic approach to evaluate the effectiveness of interventions in real-world settings [24,26]. According to the TwiCs design, eligible patients will be randomized in a 1:1 ratio to the intervention or control group (Fig 2). Patients allocated to the intervention group will be contacted by a researcher by telephone, provided with study information using a standardised script and offered a consultation with the PCCT, which they may accept or refrain from. Patients in the control group will not be informed about the trial and receive usual care. Data collected within the cohort will be used to estimate intervention effects.

**Fig 2 pone.0349792.g002:**
[figure not shown]
Participant timeline.

Randomization will be conducted using a computer-generated allocation sequence with random permuted blocks of sizes 4, 6 or 8 (Castor, Amsterdam, The Netherlands, www.castoredc.com). To ensure balance across sites, randomization will be stratified by participating center. Allocation concealment is maintained as the randomization code will only be released after the patient has been recruited into the trial.

Patients allocated to the intervention group will be informed about the intervention by the researcher, radiation oncologist or an authorized delegate, and will receive written information outlining the study procedures. Patients can accept or refrain from the intervention. If the patient needs additional time to consider participation, the researcher will contact the patient within a few days to determine whether the patient wishes to consult with a palliative care specialist of the PCCT. Patients who accept the intervention will be scheduled for an initial consultation with the palliative care specialist within two weeks after the start of radiotherapy. Informed consent will be obtained at the start of the PCCT consultation.

Blinding of researchers and clinicians to group assignment is not feasible. Patients in the control group remain blinded to group allocation and are unaware of the existence of the trial, consistent with the TwiCs design.

### Ethics and dissemination

This study falls outside the scope of the Dutch Medical Research Involving Human Subjects Act (Wet Medisch-wetenschappelijk Onderzoek met mensen, WMO) because the intervention is usual care and the randomization component is embedded within the PRESENT+ study, and therefore, formal approval of an accredited medical ethics committee is not required in the Netherlands [25,27]. However, in the UMC Utrecht, an independent quality check has been carried out to ensure compliance with legislation and regulations (regarding informed consent procedure, data management, privacy aspects and legal aspects). The main results of this study will be disseminated through publishing in peer-reviewed academic journals.

### Interventions

The palliative care consultation will be patient-centered, tailored to the wishes, needs and values of the patient, with family caregivers invited to be present and actively participate at the consultation. The palliative care consultant will conduct the consultation following their standard clinical procedures, guidelines, and practices. Before the consultation, all patients receive prepatory materials including a conversation aid and a site-specific PCCT leaflet. Furthermore, they are asked to complete a questionnaire (Utrecht Symptom Diary 4 Dimensions (USD-4D), Hospital Anxiety and Depression Scale (HADS) or Distress Thermometer), assessing the physical, psychological, social and spritiual dimensions, which serves as a guide for the consultation [28–31]. During the consultation, patients’ symptoms, wishes and needs across all four dimensions are discussed, followed by counseling and recommendations as appropriate, and referral to relevant specialists and/or follow-up of specialist palliative care if needed. The content of the consultation will be documented in the electronic health record and is accessible to both patients and their treating physician. In addition, the patients’ general practitioner will be notified of the consultation through a formal letter.

### Outcomes

The primary outcome is patient satisfaction with care, specifically focusing on the domain of affective behavior, measured four weeks after enrollment into PRESENT + . Satisfaction will be assessed using the European Organisation for Research and Treatment of Cancer (EORTC) Satisfaction with Cancer Care core questionnaire (PATSAT-C33) [32]. Patients will rate their experience on five-point Likert scales ranging from poor to excellent. The primary analysis will focus on the four-item subscale Affective Behavior. The PATSAT-C33 has been slightly adapted as participants will be asked to evaluate care provided by ‘healthcare providers in the hospital(s) in which they received oncological care’ instead of ‘nurses and radiotherapy technicians’.

Secondary outcomes will include patient-reported measures and overall survival:

Pain (response), assessed at baseline, 2, 4, 6 and 8 weeks, and at 3 and 6 months, using the Brief Pain Inventory (BPI), which has been validated in patients with painful bone metastases [33,34]. The BPI consists of 11 items addressing pain perception and interference by pain. Responses are rated on a scale from 0 (no pain/interference) to 10 (maximum pain/interference).Symptom burden, including physical, psychological, social and spiritual symptoms, will be evaluated at 4 and 8 weeks, and at 3 and 6 months, using the Utrecht Symptom Diary – four dimensions (USD-4D), a 21-item instrument [28]. Items are scored on a 11-point scale ranging from 0 (no symptom) to 10 (worst intensity).Quality of life at baseline, 4 and 8 weeks, and at 3 and 6 months using the EORTC Quality of Life Questionnaire Core 15 Palliative Care (QLQ-C15-PAL), which evaluates physical and emotional functioning, and global quality of life [35].In addition, the EORTC QLQ Bone Metastases module (BM22) will be used to assess painful sites, pain characteristics, functional interference and psychosocial aspects [36]. Responses for each scale are rated on a four-point Likert scale (from ‘not at all’ to ‘very much’), summed and transformed to a 0–100 scale. Higher scores on functioning scales indicate better functioning, whereas higher score on symptom scales represent greater symptom burden. The global quality of life item is rated on a seven-point scale (from ‘very poor’ to ‘excellent’), with a higher transformed score reflecting a better overall quality of life.Additional patient satisfaction with care outcomes including information, coordination, and overall care, using the EORTC PATSAT-C33.Overall survival.

Secondary outcomes will also include palliative care utilization, assessed as follows:

Within the intervention group, the number of patients who accept and complete the intervention (i.e., consultation with the PCCT) will be recorded, along with the documented reasons for refraining from the intervention.Specialist palliative care utilization during follow-up, defined as any contact with the hospital palliative care consultation team from randomization until death or up to two years post-randomization.Semi-structured in-depth interviews with patients who accepted the intervention will be conducted to obtain insight into experiences with the timing of the consultation and the consultation itself.

### Data collection, handling and monitoring

Consistent with the TwiCs design, data from the PRESENT+ cohort will be used for effect estimation. Patients who do not return a questionnaire within one week will receive a reminder. Patients who refrain or withdraw from the trial will continue to be followed within PRESENT + . If patients withdraw from PRESENT + , all data collected up to the point of withdrawal will be retained and included in the analyses.

De-identified data, including clinical data and data from the questionnaires, will be entered into the Castor data management system and is only accessible for investigators who are authorized to enter the system with their personal username and password. Based on the nature of the study interventions, a risk assessment has determined that risk-based monitoring is not necessary. Therefore, standard centralized oversight and routine data review are considered sufficient to ensure data quality and participant safety.

### Sample size

Based on internal observations (unpublished), we expect to enrol approximately 520 patients per year in PRESENT + . Currently, 79% of the patients participating in the PRESENT+ cohort provided consent to randomization into future intervention studies. Of those, approximately 40% are expected to meet the inclusion criteria for participation. Therefore, about 520 * 0.79 * 0.40 = 164 patients will be eligible every year for randomization in a 1:1 ratio to the intervention or control group. After 1.5 year of enrollment into the TIPZO-RT trial, we expect to have randomized 246 patients.

Of the patients offered a consultation with the PCCT, it is anticipated that 30% will refrain from the intervention. In a previous study, the mean score of patient satisfaction with care (interpersonal skills, EORTC IN-PATSAT32, which is most closely related to the primary outcome of this study (affective behavior, EORTC PATSAT-C33)) was 70.0 (SD = 21) among patients with metastatic solid tumors [37,38]. With a sample size of 246 patients, taking into account a refusal rate of 30% in the intervention group, 80% power, and a two-sided alpha of 0.05, the study is powered to detect a minimal difference of 7.6 points on patient satisfaction with care at four weeks follow-up (0.7 * 80.8 + 0.3 * 70.0).

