### Statistical analysis

A detailed statistical analysis plan will be developed and published prior to data analysis. The primary analysis will compare the intervention group to the usual care control group in terms of patient satisfaction with care, specifically focusing on the subscale affective behavior. As some patients allocated to the intervention refrain from the intervention, the statistical analysis plan will outline how such non-adherence will be accounted for using the estimand framework [39,40]. Secondary and sensitivity analyses will be specified to address alternative clinical questions and analytical scenarios.

An intermediate analysis will be performed once 40% of the total sample has been randomized. This analysis will evaluate the proportion of patients that have completed the primary outcome measurement, as well as the refusal rate in the intervention group. If the refusal rate is higher than expected (i.e., > 10%), a sample size re-estimation may be considered to increase the sample size and maintain adequate power.

Approaches to handling non-adherence will be described in the statistical analysis plan and will be aligned with the estimand. The extent and patterns of missing data will be evaluated. If appropriate, multiple imputation methods will be used to address missing data under the assumption that data is missing at random (MAR). If the primary outcome data is determined to be missing not at random (MNAR), sensitivity analyses using best–worst and worst-best case scenarios will be performed to assess the robustness of the findings.

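### The stated 80% power for 7.6 points holds only if nearly all 246 randomized patients return the four-week questionnaire; no completion assumption is given

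*Protocol article*

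**What the plan says.** All references are to the protocol article.

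- **Origin of 246 (Sample size).** The number comes from expected accrual: 520 × 0.79 × 0.40 = 164 eligible patients a year, for a year and a half. It is a count of patients randomized: "After 1.5 year of enrollment into the TIPZO-RT trial, we expect to have randomized 246 patients".
- **Power statement (Sample size).** The same 246 enters the calculation: "With a sample size of 246 patients, taking into account a refusal rate of 30% in the intervention group, 80% power", with "a two-sided alpha of 0.05". The conclusion is that "the study is powered to detect a minimal difference of 7.6 points on patient satisfaction with care at four weeks follow-up (0.7 * 80.8 + 0.3 * 70.0".
- **Refusal (Sample size).** Of the patients offered a consultation, "it is anticipated that 30% will refrain from the intervention". Under Data collection, handling and monitoring, patients who refrain are still followed in the cohort.
- **Missing outcomes.** The data collection section provides for reminders and for withdrawal from the cohort. Under Statistical analysis, an interim look at 40% randomized reviews completion of the primary outcome. The same section says that, if appropriate, "multiple imputation methods will be used to address missing data under the assumption that data is missing at random (MAR", and adds best-worst and worst-best case scenarios for data missing not at random.

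No expected completion or dropout rate is stated anywhere in the article.

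**The concern.** The sample size calculation makes one allowance, for refusal, and that acts on the size of the effect. It does not reduce the number of patients who supply a score. Non-return of the four-week questionnaire is a separate loss that can occur in both arms. The outcome is self-reported by patients with advanced cancer and symptomatic bone metastases, and the article's own data handling provisions take some non-return as given. The power statement takes it as zero.

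At stake is how far the published design figure can be relied on. A reader would take 246 randomized patients as enough for 80% power at 7.6 points, when the figure belongs to 246 completed questionnaires. Neither the estimand nor the validity of the eventual estimate is affected by this point.

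**Working it through.** **Inputs, all from the article.** Randomized N = 246, allocated 1:1 ("eligible patients will be randomized in a 1:1 ratio to the intervention or control group"), so 123 per arm; control mean and SD ("was 70.0 (SD = 21) among patients with metastatic solid tumors"); mean of 80.8 among acceptors; 30% refusal; two-sided α = 0.05; power 80%.

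**Input not in the article.** The proportion m of missing four-week scores. It is assumed below, equal in both arms, over a range of 5% to 30%.

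**Step 1: the diluted difference.** The intervention-arm mean is 0.7 × 80.8 + 0.3 × 70.0 = 77.56. The difference is 77.56 − 70.0 = 7.56, or equally 0.7 × 10.8, which rounds to the stated 7.6.

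**Step 2: reproduce the stated power.** For an unadjusted two-sample t-test, SE = SD × √(2/n). With n = 123, SE = 21 × √(2/123) = 2.678. The noncentrality is 7.56 / 2.678 = 2.823 on 244 degrees of freedom, with critical value 1.970. Power is 80.3% (80.6% by the normal approximation). The difference detectable at exactly 80% is 7.53 points. Divided by 0.7 this is 10.76 among acceptors, which matches the article's 80.8 − 70.0 = 10.8. The stated figure is therefore reproduced, with all 246 patients contributing a score.

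**Step 3: look for a hidden allowance.** Solving the same test for N at 80% power gives about 242 for 7.6 points and 244 to 245 for 7.56 points. The surplus is 246 − 242 = 4 down to 246 − 245 = 1 patient, that is 1.6% down to 0.4%. The rounding does not hide an attrition allowance.

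**Step 4: bring in missing scores.** Put n = 123 × (1 − m) per arm, keeping the true difference at 7.56 and SD at 21. For example, at m = 0.20, n = 98.4, SE = 21 × √(2/98.4) = 2.994, noncentrality = 7.56 / 2.994 = 2.525, and power = 71%.

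| Assumed missing | Analysed, total | Power for 7.56 | Detectable at 80% power | Same, among acceptors (÷ 0.7) |
|---|---|---|---|---|
| 0% | 246 | 80.3% | 7.53 | 10.8 |
| 5% | 234 | 78% | 7.7 | 11.0 |
| 10% | 221 | 76% | 7.9 | 11.3 |
| 20% | 197 | 71% | 8.4 | 12.0 |
| 30% | 172 | 65% | 9.0 | 12.9 |

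**Step 5: does the refusal allowance already cover this?** No. Refusers are counted in Step 1 with a mean of 70.0, so the calculation relies on their scores being observed, in line with their continued follow-up.

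**The case against.** The strongest replies, and what stands of each:

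- **The arithmetic is correct.** This stands in full. A reader might infer a calculation error from this point; there is none. The fault is an unstated planning assumption of complete data.
- **The size of the loss is not in the documents.** This also stands. A reader might infer that the trial has a known shortfall, for instance that its power is 71%. The article does not support that, because it gives no completion rate. Eligible patients have already consented to patient-reported data collection, reminders are sent, and four weeks is early. These features may keep the loss small, and at 5% missing power is still 78%. They do not make it zero.
- **The interim look protects power.** In part. Completion is reviewed at 40% randomized, and the same paragraph allows a sample size re-estimation to be considered. But the stated trigger is the refusal rate; no action is attached to low completion. (That trigger, above 10%, also conflicts with the expected 30% refusal. This is a separate matter that needs reconciling.)
- **Imputation or covariate adjustment may recover precision.** Possibly some, and the model is left to an analysis plan that is not shown. In general, imputation under missing at random does not restore lost information. How much it recovers depends on good predictors, and the outcomes section lists no baseline satisfaction score.
- **The analysis plan will deal with missing data.** It can fix how they are analysed. It cannot change what the published power statement assumes.

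**Conclusion.** The concern holds in a limited form. The claim of 80% power for 7.6 points is correct for about 246 completed questionnaires and is presented as a property of 246 randomized patients. The margin is 1 to 4 patients, so almost any non-return takes power below 80%.

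The direction is secure, because the article itself anticipates missing outcomes. The size is conditional: 78% to 65% power, or 7.7 to 9.0 detectable points, for assumed losses of 5% to 30%. This rests on an unadjusted t-test, equal loss in both arms, SD 21 and a true difference of 7.56. It should be fixed as a sample size assumption. It does not invalidate the design, and it does not show that the trial must be enlarged.

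**What to change.** Reword the Sample size section in one of two ways:

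1. State an expected four-week completion rate, taken from existing PRESENT+ return rates, and give the resulting power or detectable difference. As an illustration only, if completion were 80%, 246 randomized would give about 197 analysable, 80% power for 8.4 points and about 71% for 7.56.
2. Or keep the present figure and say that 80% power for 7.6 points applies to about 246 completed questionnaires, not to 246 randomized patients.

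The cost is wording, plus a look at cohort return rates for the first option. The stated figure becomes somewhat less favourable. No added patients are needed to correct the statement.
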